## Abstract

**Background:**

Borderline Personality Disorder (BPD) is a common mental disorder associated with raised mortality, morbidity and substantial economic costs. Although complex psychological interventions have been shown to be useful in the treatment of BPD, such treatments are expensive to deliver and therefore have limited availability and questionable cost-effectiveness. Less complex interventions are required for the management of BPD. A Joint Crisis Plan (JCP) is a record containing a service user's treatment preferences for the management of future crises and is created by the service user with the help of their treating mental health team. These plans have been shown to to be an effective way of reducing compulsory treatment in people with psychosis. However, to date they have not been used with individuals with BPD. This exploratory trial will examine whether use of a JCP is an effective and cost-effective intervention for people with BPD for reducing self-harm.

**Methods/Design:**

In this single blind exploratory randomized controlled trial, a total of 120 participants (age >18 years with a primary diagnosis of DSM-IV borderline personality disorder) will be recruited from community mental health teams and, after completing a baseline assessment, will be assigned to one of two conditions: (1) a Joint Crisis Plan, or (2) treatment as usual. Those allocated to the JCP condition will take part in a facilitated meeting, the purpose of which will be to agree the contents of the plan. Following the meeting, a typed version of the JCP will be sent to the patient and to any other individuals specified by the participant. All participants will be followed-up at 6 months. The primary outcome measures are: any self-harm event, time to first episode of self-harm and number of self-harm events over the follow-up period. Secondary outcome measures are length of time from contemplation to act of self-harm, help-seeking behaviour after self-harm, cost, working alliance, engagement with services and perceived coercion. Other outcome variables are quality of life, social impairment and satisfaction with treatment.

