### Sample size

#### Assumptions

For the purposes of the power calculation, the proportion of participants self-harming within the two groups has been chosen as the primary outcome, as this is likely to be the most consistent across the data collection methods, the most complete, and is more amenable to cost-effectiveness analysis. In a previous large RCT (the POPMACT trial) of cognitive therapy versus TAU for people who self-harmed, 36% of patients in the TAU group had a self-harm episode over the first 6 months of the trial [24]. We envisage that the incidence of self-harm in our TAU will be similar to the POPMACT trial. In an RCT of 'green cards' versus TAU for first presentation self-harm, the risk of self-harm after randomisation in the green card group was 37% (95%CI 14% to 97%) of the risk in the TAU group [25]. Given that the green card is not individualised whereas JCPs will be, it will be assumed that the JCP intervention would result in a larger effect, with a lower proportion (one third) of individuals at risk of self-harm since randomisation (33%).

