### Statistical analysis plan

An intention-to-treat analysis will be applied in the first instance (i.e. analysing all available data from randomised participants). The three data collection methods for the outcome of self-harm (i.e., participant interviews, diaries and electronic case records) are likely to differ on the amount of missing data. We will compare proportions of missing data using chi-square tests and agreement between data collection methods using Lin's Concordance Correlation Coefficient. Preliminary effectiveness estimates: Logistic regression will be used to compare proportions of patients that have self-harmed during the follow-up period in the two groups. Analysis of 'time to first self harm' outcome will also be conducted using survival analysis methods; log-rank test for bivariate comparisons and cox's proportional hazards to adjust for gender, stratification variables and time spent on treatment prior to randomisation. Other outcome assessments (continuous and binary) will be compared between the treatment groups at 6-month follow-up using t-tests, chi-square tests or non-parametric equivalents as appropriate, and regression modelling. The primary outcome analysis will be repeated on all three outcome collection methods to determine if conclusions remain the same. We expect little disparity in reporting of 'any self-harm episode' but potentially more in the time of first episode and number of episodes. If conclusions differ by the collection method used we will investigate reasons for the discrepancy. From this analysis we will be more certain of the appropriate collection methods for self-harm data and be better placed to decide on the appropriate outcome measure and estimate effectiveness in a future definitive trial.

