### Economic evaluation

The economic evaluation will take a broad perspective, including the cost of all hospital and community health and social care services and contacts with the criminal justice system. Resource use information will be collected using a modified version of the Adult Service Use Schedule (AD-SUS) [23]. These data will also allow us to record what TAU was actually delivered during the trial. Resource use data will be combined with appropriate national unit costs to calculate the total cost of the intervention and control groups. The cost of the JCP will be directly calculated from salaries using a micro-costing approach [26]. Differences in mean total costs between groups will be compared using the standard t-test with ordinary least squares regression used for adjusted analyses and the validity of results confirmed using bootstrapping [27]. The cost-effectiveness of the intervention will be assessed through the calculation of incremental cost effectiveness ratios, using the primary outcome measure and cost-utility will be assessed through the calculation of QALYs based on the EQ-5D. Uncertainty around the cost and effectiveness estimates will be represented using cost-effectiveness acceptability curves [28].

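### The protocol lists three primary outcomes in the abstract but one elsewhere, and names no lead data source for self-harm, so no single result is fixed in advance

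*Protocol article*

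**What the plan says.** On the number of primary outcomes:

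- Abstract, Methods/Design: "The primary outcome measures are: any self-harm event, time to first episode of self-harm and number of self-harm events over the follow-up period".
- The sample-size section, under its Assumptions heading, opens with: "For the purposes of the power calculation, the proportion of participants self-harming within the two groups has been chosen as the primary outcome". The reasons given are consistency across collection methods, completeness and suitability for the economic analysis.
- Power calculation: 114 participants, raised to 120, for 36% against 12% at two-sided 5% and 80% power. A second calculation covers time to first event (hazard ratio 0.29, 10% dropout).
- Economic evaluation: "incremental cost effectiveness ratios, using the primary outcome measure", in the singular. The Discussion also refers to the choice of primary outcome in the singular.

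On the data source, the Statistical analysis plan section lists "participant interviews, diaries and electronic case records" and continues: "The primary outcome analysis will be repeated on all three outcome collection methods to determine if conclusions remain the same". If the sources disagree: "If conclusions differ by the collection method used we will investigate reasons for the discrepancy". No source is named as leading.

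**The concern.** Aim 1 is worded as determining whether joint crisis plans benefit self-harming behaviour, and aim 2 concerns cost-effectiveness. Both need one effect estimate agreed before the data are seen. As written, a reader cannot tell whether that estimate is a difference in proportions, a hazard ratio or a comparison of counts, nor whether it comes from the interview, the diary or the record. If the sources or outcomes disagree, the choice of which to headline would be made after seeing them. The denominator of the cost-effectiveness ratio is open in the same way.

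The sample size is affected too. The increase from 114 to 120 allows for loss in administrative data, while the time-to-event calculation assumes 10% dropout. Which allowance is relevant depends on a source that has not been chosen.

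**Working it through.** **1. The texts side by side.** Three primaries (Abstract), one for the purposes of power (Assumptions), one (Economic evaluation, Discussion). The Statistical analysis plan section gives logistic regression for any self-harm and survival methods for time to first episode. It names no specific method for the number of events, which falls under the general sentence on other outcomes although the abstract calls it primary. These statements cannot all describe the same plan.

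**2. The plan's own sample size.** Inputs from the Power calculation: p1 = 0.36, p2 = 0.12, two-sided 5%, 80% power; hence mean proportion 0.24 and difference d = 0.24.

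- Uncorrected: n0 = [1.96 × √(2 × 0.24 × 0.76) + 0.842 × √(0.36 × 0.64 + 0.12 × 0.88)]² / 0.24² = (1.184 + 0.488)² / 0.0576 = 48.5, so 49 per arm, 98 in total.
- With continuity correction: n = (n0/4) × [1 + √(1 + 4/(n0 × d))]² = 56.5, so 57 per arm, 114 in total. This reproduces the plan.
- Loss: 114/0.95 = 120.
- Time to event: ln(0.88)/ln(0.64) = 0.286, in line with 0.29. The Freedman formula gives 26 events; 26/0.24 = 108; 108/0.9 = 120.

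Each figure is correct for one test at 5%.

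**3. What the lead source does to power.** Power = Φ{[d − 1/n − 1.96 × √(2 × 0.24 × 0.76/n)] / √[(0.36 × 0.64 + 0.12 × 0.88)/n]}, leaving out 1/n for the uncorrected test.

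| Analysed per arm | Continuity-corrected | Uncorrected |
|---|---|---|
| 57 (120 less 5%) | 80.4% | 86.1% |
| 54 (120 less 10%) | (0.2215 − 0.1611)/0.0789 = 0.766, so 77.8% | (0.24 − 0.1611)/0.0789 = 1.00, so 84.1% |

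**4. False-positive chance if any unadjusted positive result counted as success.** Independent tests would give 1 − 0.95³ = 14.3% for three and 1 − 0.95⁹ = 37.0% for nine. These are ceilings, because the outcomes derive from the same events and the sources record the same behaviour. Two null simulations used 60 per arm, 36% with any event and overdispersed counts (shape 0.3). The shape and the share of events each source captures are assumptions.

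| Reading | Unequal capture (90/80/50% or 80/60/30%), t-test on counts, 3,000 trials | Equal capture 100/90/70/50%, rank test on counts, 4,000 trials |
|---|---|---|
| Three outcomes, one source | 8-9% | about 6-7% |
| Any self-harm, three sources | 9-11% | 5.0/7.2/10.5/12.3% |
| All nine tests | 13.5-16% | 6.9/9.3/12.2/13.4% |

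**5. Cost of keeping three primaries.** With Bonferroni at 0.05/3, the continuity-corrected method needs 148 evaluable participants. At 57 per arm, power for any self-harm falls from 80% to 66%.

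**The case against.** The trial is declared exploratory and not definitive, its effectiveness results are labelled preliminary, and comparing collection methods is one of its stated purposes. The repetition across sources is written as a check that conclusions agree, and a conflict is meant to inform the choice of outcome and collection method for a later trial. The authors also state: "We expect little disparity in reporting of 'any self-harm episode' but potentially more in the time of first episode and number of episodes". If that holds, the sources will be close to interchangeable for the outcome that was powered. All of this stands, and it lowers the consequence.

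A reader might infer that the plan runs nine primary tests and that its error rate is therefore far above the stated 5%. The protocol does not support this. The 5% is the level of one test in the power calculation, and no family-wise rate is claimed. No sentence says that any one positive result counts as success. Nine tests follow only if all three outcomes are primary and each source's result counts separately.

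A reader might also infer that the blinded interview is the obvious lead source. The documents do not settle that: the loss allowance refers to administrative data, and records are to be obtained even for participants lost to the interview. Nor do they establish that records mainly capture self-harm that reaches services; that is inference.

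What the objection does not remove is the contradiction itself. An exploratory trial with an effectiveness aim, a powered comparison and a cost-effectiveness ratio still has to say which estimate is primary, and a consistency check needs a reference result to check against.

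**Conclusion.** The protocol contradicts itself on the primary outcome and leaves the lead source for self-harm open, so no outcome-source result is fixed in advance for aim 1 or for the cost-effectiveness ratio. This conclusion rests on the text alone.

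The error-rate figures are conditional. Under an any-positive reading, which the plan does not adopt, they run from roughly 6-9% (three outcomes, one source) to roughly 7-16% (nine tests), and they depend on capture rates and a count distribution that the protocol does not give. The independence figures of 14% and 37% should not be used to describe this plan.

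Severity: should be fixed. The exploratory status keeps it below a must-fix.

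**What to change.** - State in the Abstract, Sample size, Statistical analysis plan and Economic evaluation sections that any self-harm from randomisation to 6 months (yes/no) is the single primary outcome. The Assumptions section already argues for it.
- Make time to first episode and number of events secondary.
- Name one lead data source before unblinding, with the other two as named sensitivity analyses. The comparison of collection methods is then kept in full.
- Use the same outcome and source in the incremental cost-effectiveness ratio.
- Carry the source into the Power calculation. If case records lead with about 5% loss, 114/120 stands. If the interview leads with 10% dropout (54 per arm), restate power as about 78% by the continuity-corrected method, or 84% uncorrected, and say which method is used.

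The choice of source belongs to the investigators. Records cover participants lost to interview, but a copy of the plan is filed in the same electronic record, so extraction could reveal allocation. The interview is blinded but exposed to dropout.

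The cost is mainly wording, plus revised sample-size text if the interview leads. The small downside is that results on the other outcomes and sources become supportive only.

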**Discussion:**

Results of this trial will help to clarify the potential beneficial effects of JCPs for people with BPD and provide information to design a definitive trial.

**Trial Registration:**

Current Controlled Trials ISRCTN12440268

## Background

Borderline personality disorder (BPD) is characterised by a pervasive pattern of instability in emotional regulation, impulse control, interpersonal relationships, and self-image [1]. The condition occurs globally with a community prevalence of 0.7%, although the prevalence is far higher in clinical populations where it affects up to 20% of psychiatric outpatients [2] and is associated with high rates of co-morbidity and significantly increased health service costs [3,4]. People with BPD are more likely to experience adverse life events and their ability to cope with such events is impaired by poor problem-solving skills [5]. Self-harm is often employed by people with BPD as a way of regulating their level of arousal at times of crises, however, such behaviour puts them at increased risk of suicide [6].

A Joint Crisis Plan (JCP) is a record containing a service user's treatment preferences for the management of future crises. It is developed by a mental health service user in collaboration with staff and aims to increase the service user's level of involvement in their own treatment [7]. Held by the service user, it contains his or her treatment preferences for any future psychiatric crisis, when he or she may be less able to express clear views. The JCP is created at a meeting between the service user, those involved in his or her care, and an independent facilitator not involved in the service user's care. The service user is provided with a template (a list of subheadings the service user may or may not wish to include in the plan) and the team then openly discusses with the service user the advantages and disadvantages of the various subheadings included. The JCP is therefore produced collaboratively between the service user and his or her treating team with the aim of the plan being consulted and followed during a future crisis. JCPs improve the information available to clinical staff about the management of a crisis and empower service users by ensuring that they are actively involved in the generation of their own crisis plan. JCPs have been shown to be an effective way of reducing compulsory treatment in people with psychosis [8], help service users feel more in control of their mental health problems [9] and may also reduce admission rates to hospital [10].

The treatment of people with BPD is frequently characterized by conflicts with health professionals and such conflicts are particularly likely to arise in the management of self-harming behaviour [11]. Moreover, the cessation of self-harming behavious is often associated with an individual's ability to assert greater control over their life [12]. Given that the JCP is designed to facilitate a more collaborative relationship with staff, we hypothesise that JCPs may be an effective way of managing self-harm in people with BPD. In this article, we describe the proposed methods of an exploratory randomized controlled trial (RCT) that is designed to estimate the effectiveness and cost-effectiveness of JCPs on self-harming behaviour in people with BPD and to determine the most effective methods of data collection to inform future studies.

## Methods/Design

### Overview

The "Joint crisis plans for people who **S**elf-**H**arm" (JOSHUA) study is a single centre exploratory randomized controlled trial of JCPs compared with a treatment as usual control condition for people with BPD and a history of self-harming behaviour. The total duration of the study will be two years, to allow for the recruitment to target numbers of participants, provision of the intervention, follow-up assessments, and data analysis, using intention-to-treat methods.

### Aims

The JOSHUA study has the following aims:

1. To determine whether JCPs for people with BPD have a beneficial effect on self-harming behaviour, and to estimate the likely range of effects consistent with the use of JCPs.

2. To determine the cost-effectiveness of JCPs for people with BPD.

### Eligibility criteria

#### Inclusion criteria

i) Age greater than or equal to 18 years

ii) Current contact with a Community Mental Health Team (CMHT)

iii) A primary diagnosis of DSM-IV Borderline Personality Disorder

iv) An episode of self-harm in the previous year

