### Randomisation procedure and methods to minimise bias

Participants will be randomised using the method of minimisation with a random component stratified by alcohol misuse [as measured by the Alcohol Use Disorders Identification Test (AUDIT) [13]] and depression [as measured by the Hospital Anxiety and Depression Scale (HADS) [14]]. The randomisation will be managed by the Clinical Trials Unit (CTU) at the Institute of Psychiatry. Confirmation of eligibility, consent, and baseline data will be obtained prior to randomisation. Bias in the recruitment and randomisation process will be avoided by having randomisation done centrally by the CTU, and hence concealment maintained from the investigators, and by keeping a log of all service users randomised and including them all in the analysis. The research worker collecting outcome data will be blinded to the allocation. Some outcome data will be obtained from electronic patient records, even for participants lost to follow-up interview. This will include any episodes of self harm, hospital admissions and service use recorded in the electronic records. Bias in the collection of outcome data will also be minimised by the use of standardised objective assessments and by blinding the researchers as far as possible to service user allocation. There will be specific instructions to participants and clinical teams not to disclose the treatment details of any study participant. Every effort will be made to maximise the single blindness of research workers, whose 'best guesses' of treatment arm status will be assessed after the final assessment in order to test whether their blindness was successfully maintained.

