### Assessments

#### Baseline assessments

(i) Socio-demographic details - age, sex, ethnicity, employment, educational, marital status

(ii) Details of self-harming behaviour over the preceding 6 months - measured using questions from Hawton et al [15]

(iii) Personality disorder status - Structured Clinical Interview for DSM-IV personality disorders (SCID-II) [16] - BPD subsection

(iv) Functional impairment - Work & Social Adjustment Schedule (WSAS) [17]

(v) Engagement with services - Service Engagement Scale [18]

(vi) Working Alliance - Working Alliance Inventory- Short Form (client version) (WAI-S) [19]

(vii) WAI-S (therapist version)

(viii) Health-related quality of life - Euroquol (EQ-5D) [20]

(ix) Satisfaction with care - Client Satisfaction Questionnaire (CSQ) [21]

(x) Perceived coercion - Treatment Experience Scale [22]

(xi) Service use - Adult Service Use Schedule (ADSUS) [23]

(xii) Alcohol use - Alcohol Use Disorders Identification Test (AUDIT) [13]

(xiii) Illicit substance use - Questionnaire on use of illicit substances taken over last year

(xiv) Emotional symptoms - Hospital Anxiety and Depression Scale (HADS) [14]

Additionally, socio-demographic data and length of practice data will be collected for care coordinators, using a proforma developed during the previous pilot work.

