#### Follow-up assessments

Six months after randomisation, all participants will be followed-up. A research worker, blinded to treatment allocation, will arrange a convenient time to meet with the participant in order to complete the following measures:

i) Time to first act of self-harm (if any)

ii) Number of self-harm episodes over the preceding 6-month period

iii) Regarding the most recent act of self-harm - length of time from contemplation of self-harm to self-harm act

iv) Regarding the most recent act of self-harm - help-seeking behaviour prior to event (see 10.3)

v) WAI-S (client + therapist)

vi) WSAS

vii) Service Engagement Scale

viii) Treatment Experience Scale

ix) EQ-5D

x) CSQ

xi) ADSUS

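### Self-harm in the 6 months before baseline is recorded before randomisation and matches the outcome window, but is neither a minimisation factor nor a listed Cox covariate

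*Protocol article*

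**What the plan says.** All references are to the Protocol article.

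- **Inclusion criteria**, item iv: "An episode of self-harm in the previous year". The exclusion criteria add nothing about how recent or frequent self-harm must be, and state that entry is kept broad for external validity.
- **Baseline assessments**, item ii: "Details of self-harming behaviour over the preceding 6 months".
- **Follow-up assessments**, item ii: "Number of self-harm episodes over the preceding 6-month period". The Sample size section takes the proportion self-harming as the primary outcome for the power calculation, with 36% expected under usual treatment and 12% with the Joint Crisis Plan (JCP).
- **Randomisation procedure and methods to minimise bias**: "Participants will be randomised using the method of minimisation with a random component stratified by alcohol misuse", with HADS depression as the second factor. No third factor is named. On timing: "Confirmation of eligibility, consent, and baseline data will be obtained prior to randomisation".
- **Statistical analysis plan**: "Logistic regression will be used to compare proportions of patients that have self-harmed during the follow-up period in the two groups", with no covariates stated. For time to first self-harm, the model is "cox's proportional hazards to adjust for gender, stratification variables and time spent on treatment prior to randomisation".

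**The concern.** The trial measures the pre-randomisation counterpart of its own main outcome, over a window of the same length and in time for the trials unit to use it. The allocation scheme does not use it, and neither does the one covariate list that the article gives.

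The 12-month entry rule makes this matter. A person whose last episode was 7 to 12 months ago is eligible and has already gone longer than the whole follow-up without an event. That person enters beside others who self-harm often. If the two kinds of entrant differ in risk, which is likely but not shown in the documents, a chance difference in their shares between arms carries straight into the estimated effect.

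The first aim includes estimating the range of effects consistent with the intervention, and the results are meant to inform a definitive trial. Avoidable noise in that estimate is therefore worth removing if removal is cheap.

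**Working it through.** **1. The plan's own figures.** With 36% v 12%, two-sided 5% and 80% power, the mean proportion is 0.24:

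n = [1.96·√(2·0.24·0.76) + 0.8416·√(0.36·0.64 + 0.12·0.88)]² / 0.24² = 48.5, so 49 per arm.

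The continuity correction, (n/4)·[1 + √(1 + 4/(n·0.24))]², gives 56.5, so 57 per arm and 114 in total. This matches the plan. The hazard ratio also matches: ln 0.88 / ln 0.64 = 0.286, or 0.29. No stated figure is wrong on this point.

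**2. Chance imbalance.** Let q be the share of the 120 entrants with self-harm in the last 6 months. The documents do not give q, so 50% to 90% is assumed. If 60 of 120 go to each arm with no balancing on this factor, the number of recent self-harmers in one arm is hypergeometric. The SD of the difference in shares is 2·√(q(1−q)/119).

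**3. Effect on the risk difference.** Assume recent self-harmers have RR = 2 to 4 times the risk of the others, with 36% overall. The lower risk is p₀ = 0.36/(q·RR + 1 − q), and the gap is (RR − 1)·p₀. An imbalance d moves the risk difference by d × gap if the gap is the same in both arms. Example: q = 0.5 and RR = 3 give 18% and 54%, so d = 10 points moves it by 0.10 × 36 = 3.6 points.

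| q | SD of difference | P(≥10 points) | P(≥20 points) | Shift from a 10-point imbalance, RR 2 to 4 |
|---|---|---|---|---|
| 50% | 9.2 | 36% | 4.4% | 2.4 to 4.3 |
| 70% | 8.4 | 32% | 2.8% | 2.1 to 3.5 |
| 80% | 7.3 | 25% | 1.1% | 2.0 to 3.2 |
| 90% | 5.5 | 13% | <0.1% | 1.9 to 2.9 |

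For q = 90%, the last column is 0.10 × 0.36/1.9 = 1.9 and 0.10 × 3 × 0.36/3.7 = 2.9 points.

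**4. The same shift under the planned effect.** If the JCP cuts every risk to one third, the gap in that arm is also one third. With the imbalance split evenly between arms, the shift is d × (gap + gap/3)/2, or two thirds of the table value. For illustrative risks of 55% and 17% (36% at a 50:50 mix), the gap is 38 points, and the shift is 0.10 × (38 + 12.7)/2 = 2.5 points. The standard error of the planned difference is √(0.36·0.64/60 + 0.12·0.88/60) = 7.5 points, so this is about a third of a standard error.

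**5. Error rate and power.** In 4,000 simulated trials per setting (60 per arm), an unadjusted test of proportions was compared with a test stratified on recent self-harm.

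| q, RR | Type I error, unadjusted | Power, unadjusted → stratified |
|---|---|---|
| 50%, 3 | 4.7% | 89.9% → 91.6% |
| 70%, 3 | 5.4% | 90.0% → 90.5% |
| 80%, 4 | 5.1% | 88.7% → 90.0% |

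These powers exceed 80% because the tests carry no continuity correction and use 120 participants. The gain comes from using the factor in the analysis; the simulation did not minimise on it.

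**The case against.** The strongest reply is that this is ordinary sampling error. Randomisation protects the test, the confidence interval already reflects chance imbalance, and the simulated error rate stays near 5%. Broad entry is deliberate, and the trial is described as exploratory. Covariate adjustment could recover most of the loss, and the logistic covariates may be settled in an analysis plan that is not shown. Minimising on alcohol misuse and depression may also partly balance recent self-harm, so the imbalance probabilities are on the high side if these are correlated.

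Most of this stands, and it sets the size of the point. What it does not answer is narrower. The minimisation factors are fixed in the protocol, and a later analysis plan cannot change how people were allocated. The Cox covariates are given as a list, and baseline self-harm is not on it. The silence on logistic covariates is not counted here as a fault.

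A reader might infer two stronger things that the documents do not support.

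- **That the 6-month baseline item leaves criterion iv unconfirmed for people whose last episode was 7 to 12 months ago.** The randomisation section lists confirmation of eligibility separately from baseline data, so the check may be made elsewhere. The baseline self-harm questions come from a cited source that is not shown, so it cannot be said that they omit the date of the last episode.
- **That the mismatch between 12-month entry and 6-month baseline causes the mixing.** The entry rule alone does that. The 6-month item matches the outcome window, which is what makes it suitable for balancing and adjustment.

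**Conclusion.** The point holds as a modest weakness in balance and precision. A likely prognostic variable, available before allocation and matched to the outcome window, is used neither in the minimisation nor in the stated Cox adjustment. There is no contradiction, no wrong figure and no systematic bias.

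On the assumed shares and risk ratios, an imbalance of 10 points or more would arise in about 13% to 36% of trials. An imbalance of 10 points would move the risk difference by roughly 2 to 4 points with equal risk gaps in the arms, and by about two thirds of that under the planned effect. Against a planned 24 points this is unlikely to change the conclusion. If the true effect is smaller, the same shift takes a larger share of it. The power gain of about 1 to 2 points (0.6 to 1.7 in the three settings simulated) is small.

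The change is worth making because it is cheap, not because the trial is unsound without it.

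**What to change.** 1. In the randomisation section, add self-harm in the 6 months before baseline (yes/no) as a third minimisation factor. It then enters the Cox model through the existing adjustment for stratification variables.
2. In the Statistical analysis plan section, state that the logistic model is adjusted for it as well, alongside the two existing factors. Minimising on a prognostic factor without adjusting for it gives up part of the precision gained.
3. If allocation has already started, leave the scheme alone. Name the variable as a covariate in both models before outcomes are seen by arm.

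Cost: one more factor in the trials unit's program, from data already due before randomisation, with no extra participants or visits. Balance on alcohol misuse and depression becomes slightly looser. The adjusted models also carry one more parameter on about 0.36 × 60 + 0.12 × 60 = 29 expected events, which is a reason to keep the factor as a simple yes/no.
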